## Abstract

**Background:** Anxiety is one of the most frequent disorders during the perinatal stage that is associated with adverse health effects in women and their babies. In spite of this, preventive interventions during this stage are scarce. A long-distance intervention carried out during pregnancy can be an effective and accessible resource to help improve women’s emotional state. The objective of this study is to present and assess the effectiveness of a telepsychology cognitive–behavioral preventive intervention during pregnancy to manage anxiety. **Methods:** A random clinical trial will be carried out among pregnant women in Spain. The psychological intervention will take place via videoconference in seven weekly sessions, lasting one hour each, with groups of 6–8 pregnant women. Study outcomes will be collected via online questionnaires at five points in time: pre-intervention (baseline: t0), post-intervention (baseline: t1), follow-up at 1 month (t2), follow-up at 3 months (t3) and follow-up at 6 months (t4). The control group will receive usual pregnancy care (attendance at pregnancy follow-up consultations and information and answers to frequently asked questions provided by the midwife). Our primary hypothesis is that the intervention will decrease the frequency of women who present anxious symptomatology during pregnancy. The second objective is to analyze the effectiveness of this intervention to prevent depressive symptomatology during pregnancy, as well as postpartum anxiety and depressive symptomatology. The primary outcome measure is the difference in the mean anxiety score between the intervention and control groups assessed by the Edinburgh Depression Scale-Anxiety Subscale (EDS-3A), the State–Trait Anxiety Inventory (STAI) and Generalized Anxiety Disorder Screener (GAD-7) at the end of the intervention and at 1, 3 and 6 months postpartum. Generalized anxiety disorder (GAD) will be evaluated with the SCID clinical interview at the same time points. The secondary outcome will be determined by using the EPDS at the same time points. **Conclusions:** The results will determine whether a cognitive behavioral therapy applied via videoconference is well accepted by pregnant women, and if it is effective in preventing anxiety and emotional symptoms during the perinatal stage. If this intervention is an effective and useful resource among pregnant women, it can be implemented as a tool in Spanish healthcare.

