On the other hand, it is worth remembering the high comorbidity of anxiety and depression. In a review and meta-analysis whose objective was to evaluate the effectiveness of psychological interventions to reduce perinatal anxiety, it was found that psychological interventions aimed at reducing anxiety during the perinatal stage were also effective in reducing symptoms of depression [7]. This supports research suggesting that transdiagnostic interventions targeting both anxiety and depressive symptoms tailored to the perinatal period may be more beneficial than disorder-specific interventions [37] and indicates the need to create transdiagnostic interventions to address symptoms of anxiety and depression in women during the perinatal stage since these comorbidities are generally not recognized or treated [41]. Therefore, considering the high frequency with which anxiety and depression occur together, treatments should treat them simultaneously [26].

To date, there is no protocol in Spain to prevent anxiety and comorbid emotional symptomatology during the perinatal stage by means of a videoconference psychological intervention. An intervention of this type could facilitate access and be helpful to many women during this period, reducing levels of anxiety and comorbid emotional symptoms.

The primary objective of the current study is to determine whether a preventive psychological intervention is superior to the usual care during pregnancy (attendance at pregnancy follow-up consultations and information and answers to frequently asked questions provided by the midwife) to prevent anxiety symptoms during pregnancy. The secondary objective is to examine whether this same intervention is more effective than usual care in preventing depressive symptoms during pregnancy, as well as anxiety and depressive symptoms postpartum.

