### 2.3. Outcomes and Allocation of Participants to Trial Groups

#### 2.3.1. Primary Outcome

The primary outcome measure will be the difference in the mean anxiety scores between the intervention and control groups assessed by the EDS-3A, STAI and GAD-7 questionnaire before and at the end of the intervention, and one month, 3 months and 6 months after the intervention. Generalized anxiety disorder (GAD) will also be evaluated through the DSM-5 clinical interview at the same time points. In this case, the percentages found will be compared.

The Edinburgh Depression Scale-Anxiety Subscale (EDS-3A) is the anxiety subscale of the Edinburgh Postnatal Depression Scale (EPDS) [42]. Different studies, e.g., [43,44] have found that three items (3, 4, 5) can detect anxiety in women during the perinatal period. Each of the three items has four response options (0 = none, 1 = somewhat, 2 = quite a bit, and 3 = a lot). The total score of the subscale ranges from 0 to 9. The cut-off point used in the EDS-3A to detect anxious symptomatology will be ≥5 [45].

The State–Trait Anxiety Inventory (STAI) [46] assesses both the current level of anxiety and the individual’s predisposition to suffering from anxiety. It consists of 40 items, 20 of which refer to the state subscale (STAI-E), with the other 20 referring to the trait subscale (STAI-R). The score for each subscale ranges from 0 to 60, with higher scores indicating higher levels of anxiety. In this case, the State Anxiety Subscale (STAI-E) will be applied; the recommended cut-off point for women is greater than 31 (75th percentile).

Generalized Anxiety Disorder Screener (GAD-7) [47] is a self-administered instrument consisting of seven items with four response options. The total score ranges from 0 to 21, with the highest scores being the most severe. The GAD-7 has been validated for use in Spanish-speaking pregnant women [48]. The cut-off point used to detect anxiety symptoms will be ≥7 [49].

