### 2.8. Analysis Plan

The primary analysis will compare the mean scores of EDS-3A, STAI-E and GAD-7 between the two groups before and after the intervention and one month, 3 months and 6 months after the end of the intervention to evaluate the effectiveness of the protocol in preventing anxiety symptoms. Similar analyses will be performed for the secondary result on depressive symptomatology. For the GAD, the frequencies in the two groups will be compared at the same evaluation periods.

Regarding the effectiveness of treatment, descriptive statistics will be calculated for all questionnaires. Variance analyses for repeated measurements will be performed to compare the differences between each initial score obtained with the different administered questionnaires and the scores at T1 (end of treatment), T2 (after 1 month), T3 (after 3 months) and T4 (after 6 months) will be evaluated. Bonferroni post hoc comparisons will also be conducted. The number of evaluations compared will need to be taken into account to adjust the *p*-value in the Bonferroni test with the aim of minimizing type 1 errors. The treatment effect will be calculated using Cohen’s d for each of the follow-up times. The Reliable Change Index will be calculated for each time in order to determine any significant clinical changes occurring in each individual case post-treatment. To compare differences in GAD, the chi-square test and Fisher’s exact test will be used in the contrast of 2 × 2 tables. In addition, Cochran’s Q test will be used to determine the existence of differences across time points and McNemar’s test will be used to compare the differences in categorical variables between time points in a paired manner.

Data will be analyzed using the Statistical Package for Social Science (SPSS) for Windows version 23.0.

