## 3. Intervention

### 3.1. Rationale

The intervention was based on the principles of cognitive–behavioral therapy (CBT) and transdiagnostic treatments for emotional problems and includes three sections that address the main components of CBT: thoughts, pleasant activities and social contacts. CBT is one of the interventions that has obtained the best results for the treatment and prevention of perinatal anxiety [7,52,53]. On the other hand, transdiagnostic interventions may be more beneficial than specific interventions for each disorder, as scientific evidence suggests [7,37]. The need to develop this perinatal anxiety prevention program aimed at pregnant women is justified by the high prevalence of anxiety in the perinatal stage, as well as its possible consequences for both the mother and the baby [8,54]. Furthermore, there is a high comorbidity between symptoms of perinatal depression and anxiety [6], which indicates the importance of having a transdiagnostic intervention. Another aspect that highlights the need for a program of this type is the scarcity of existing psychological interventions to treat anxiety during pregnancy and postpartum [8,55]. A prevention program has been chosen because it would allow anxiety to be treated before it becomes a problem for the mother and her baby and would prevent future suffering [26]. Specifically, it would be a universal prevention program intended for all pregnant women regardless of whether or not they are at risk of anxiety. These programs have the advantage of increasing awareness about perinatal mental health as they provide information about its prevalence and risk factors, as well as tools to cope with emotional distress and increase the support network.

A CBT prevention program has been selected for development because it is found to obtain some of the best results in clinical practice [7,24]. The techniques included in the program, such as cognitive restructuring, behavioral activation or social support, have been selected because they repeatedly appear in the reviewed interventions that have shown greater effectiveness [7,8,24,32]. It should be noted that the intervention will not exclusively address anxiety, but also depression, due to the high comorbidity they present [6].

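### The primary hypothesis concerns how many women are anxious, but the primary outcome, primary analysis and sample size concern mean scores

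*Protocol article*

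**What the plan says.** The Abstract gives the hypothesis as a frequency: "Our primary hypothesis is that the intervention will decrease the frequency of women who present anxious symptomatology during pregnancy". The primary objective in the Introduction is superiority over usual care "to prevent anxiety symptoms during pregnancy".

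The same abstract then defines the outcome as a mean: "The primary outcome measure is the difference in the mean anxiety score between the intervention and control groups". Section 2.3.1 repeats this, and section 2.8 fixes the analysis accordingly: "The primary analysis will compare the mean scores of EDS-3A, STAI-E and GAD-7 between the two groups". Section 2.7 sizes the trial on Cohen's d = 0.55 with α = 0.05 and 80% power, giving 53 per group and a recruitment target of 140. Section 2.2 allocates 2:1.

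Section 2.3.1 also gives thresholds that would classify women as anxious. For EDS-3A: "The cut-off point used in the EDS-3A to detect anxious symptomatology will be ≥5". For GAD-7: "The cut-off point used to detect anxiety symptoms will be ≥7". For STAI-E the recommended cut-off is above 31. Section 2.8 attaches no between-group comparison to these thresholds. The frequency comparison it does state is for GAD by clinical interview: chi-square or Fisher's exact test between groups, with Cochran's Q and McNemar's test across time points.

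**The concern.** A hypothesis about how many women are anxious is answered by a difference or ratio of proportions. The plan's primary outcome, analysis and power answer a different question: whether average scores differ. Carried out as written, the trial gives its stated primary hypothesis no matching primary analysis.

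Two consequences follow. First, a difference in means does not show how many women cross a threshold. It could come from small changes across the whole range, or from improvement among women who were already symptomatic. Reporting it as fewer anxious women, or as cases prevented, would go beyond what was estimated. Second, the 80% power does not carry over to the frequency claim. A reader who connects the abstract's hypothesis with section 2.7 would take the frequency comparison to be adequately powered, and it is not.

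**Working it through.** **1. The plan's own figure.** Inputs from section 2.7: d = 0.55, α = 0.05, power 80%. The sides of the test are not stated.

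- Normal approximation, two-sided, 1:1: n = 2 × (1.960 + 0.842)² / 0.55² = 51.9, so 52 per group.
- Two-sample t-test, two-sided, 1:1: 52.87, so 53 per group. This matches.
- One-sided, normal approximation: 41 per group. This does not match.

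The stated 53 is therefore a calculation for a difference in means.

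**2. Group sizes for the frequency question.** The lower bound is 2 × 53 = 106 women analysed, which at 2:1 is about 71 intervention and 35 control. The upper bound is all 140, about 93 and 47.

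**3. Assumed control frequency.** 16.8% to 19.5%, the Spanish prevalence in the Introduction. This is an assumption. The article does not tie that range to the cut-offs in section 2.3.1, and it says itself that prevalence varies with instrument and cut-off. Expected symptomatic women in the control arm: 0.168 × 35 = 5.9 up to 0.195 × 47 = 9.2.

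**4. Assumed intervention frequency, two scenarios.**

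- Halving (not in the article): 8.4% and 9.75%.
- A shift of d = 0.55 on a normal scale: Φ(Φ⁻¹(0.168) − 0.55) = Φ(−0.962 − 0.55) = 6.5%, and Φ(Φ⁻¹(0.195) − 0.55) = Φ(−0.860 − 0.55) = 7.9%.

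**5. Power.** Arcsine method, two-sided 0.05: h = 2·arcsin√p_C − 2·arcsin√p_I, and power ≈ Φ(h / √(1/n_C + 1/n_I) − 1.96). The factor 1/√(1/n_C + 1/n_I) is 4.84 for 35/71 and 5.59 for 47/93.

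| Control vs intervention | h | 35/71 | 47/93 |
|---|---|---|---|
| 16.8% vs 8.4% (halving) | 0.257 | 24% | 30% |
| 19.5% vs 9.75% (halving) | 0.280 | 27% | 35% |
| 16.8% vs 6.5% (d = 0.55) | 0.328 | 36% | 45% |
| 19.5% vs 7.9% (d = 0.55) | 0.344 | 38% | 48% |

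A pooled z-test gives slightly higher values: 27% to 38% for halving and 40% to 52% for the d = 0.55 shift. For comparison, the t-test on means with d = 0.55 at 2:1 has about 75% power with 106 women and 86% with 140.

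**6. Does the GAD comparison fill the gap?** Section 2.3.1 requires anxiety on most days over the last six months for a GAD diagnosis. That is narrower than scoring above a screening cut-off, and section 2.7 does not size the trial for it.

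**The case against.** The strongest reply is that the plan does compare an anxiety frequency between arms: GAD percentages appear under the primary outcome heading and have a named test. That stands. A reader might infer that the frequency idea is never tested at all, and the article does not support that. What remains is that GAD is a different and narrower quantity than the symptomatology in the hypothesis, and is not powered.

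A second tempting reading is that enrolling women who are already anxious defeats a prevention trial. The article does not support that either. Its hypothesis, as worded, is about how many women present symptoms, which can be read as prevalence. Comparing prevalence between randomised arms is valid because baseline cases are balanced in expectation. Section 3.1 openly describes a universal programme, "intended for all pregnant women regardless of whether or not they are at risk of anxiety". Equating prevention with new onset would be an outside definition. The narrower caution still holds: a lower mean does not by itself show fewer anxious women or fewer new cases.

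Third, McNemar's test and the Reliable Change Index look at individual change. They do, but McNemar's test is paired over time and the index is computed for each woman. Neither is stated as a between-group comparison of proportions above a cut-off.

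Fourth, the power figures depend on assumptions. That is fair, so two effect scenarios and two sample sizes are shown. Section 2.3.1 describes the STAI-E cut-off as the 75th percentile. At a control frequency of 25%, the d = 0.55 shift gives about 43% to 54%, still below 80%.

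Finally, a separate analysis plan may add proportions. It could not remove the mismatch, because the article itself states both the hypothesis and the primary outcome.

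**Conclusion.** The concern holds as a mismatch between the stated hypothesis and everything built to answer it. The hypothesis is a frequency. The primary outcome, primary analysis and sample size are about means, and the cut-offs enter no stated between-group comparison. The 80% power belongs to a mean difference only. For the frequency, 106 to 140 women at 2:1 give about 24% to 35% power for an assumed halving and about 36% to 48% for the shift implied by d = 0.55 (arcsine, two-sided 0.05). These figures rest on a control frequency of 16.8% to 19.5% and, for the second scenario, on a normal latent scale. The planned mean-score comparison itself is not faulted here. The defect is what it would be taken to show.

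**What to change.** - Restate the primary hypothesis as a lower mean anxiety score at the end of the intervention (t1), in line with the outcome and the power calculation.
- Add a secondary between-group risk difference with 95% CI for scoring above each stated cut-off (EDS-3A ≥5, STAI-E >31, GAD-7 ≥7) at t1, adjusted for baseline score, in all randomised women. Repeat it descriptively in women below the cut-off at baseline.
- State that the 80% power does not cover the frequency result.
- Do not report a lower mean alone as fewer anxious women or as new cases prevented.
- Do not add a new-case GAD analysis at t1. The intervention starts 4–6 weeks after the initial evaluation and has seven weekly sessions, so t1 falls about 10–13 weeks after baseline. A diagnosis needing six months of symptoms and first made at t1 would reach back before baseline, so it is not onset.

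Cost: a wording change and one secondary analysis on questionnaires already scheduled at t0 and t1, with no new data collection. The downside is that the frequency result becomes explicitly secondary and will be imprecise.

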## 1. Introduction

Anxiety is one of the most frequent disorders during the perinatal stage. Its prevalence is between 15% and 23% [1,2,3,4] during the pregnancy and between 3.7% and 15.0% [1,5] during postpartum. In Spain, the prevalence of anxiety ranges from 16.8 to 19.5% throughout pregnancy [3]. Additionally, one in ten women will experience comorbid anxiety and depression during pregnancy and one in twelve during the postpartum period [6]. The disparity in prevalence may be due to the moment of evaluation, the use of different evaluation instruments and cut-off points and cultural differences in relation to the importance given to mental health in a specific country and/or culture. Although its prevalence is high, research on treating anxiety during this period is recent [7,8].

Perinatal anxiety is associated with adverse health effects in women and their babies. Regarding mothers, it has been associated with an increased probability of developing postpartum depression [9], a higher risk of preeclampsia, obstetric complications and bonding problems [10,11,12]. As for newborns, they have been found to be more likely to have lower birth weight and poor cognitive development, among others [13,14], hence the importance of detecting and intervening early in prenatal anxiety to promote the well-being of mothers and children, because despite the negative consequences associated with perinatal anxiety, the majority of women are not identified or treated [7,15], as less than 15% receive treatment [16]. Given the high prevalence of prenatal anxiety and the potential for adverse consequences, early treatment is recommended [17,18]. Evidence on the effectiveness of psychological interventions during pregnancy is scarce [17,18,19,20], highlighting the importance of having specific interventions.

The need for greater access to psychological therapies has been highlighted by international institutions [17,20,21]. It must be taken into account that a non-pharmacological approach should be adopted in this period, due to the potential risks of using medications during pregnancy [22]. Furthermore, women prefer psychological interventions [23]. The National Institute for Health and Clinical Excellence [17] recommends psychological interventions, such as cognitive behavioral therapy, as a first-line treatment for mild and moderate prenatal anxiety. Early detection of anxiety symptoms in the perinatal stage can help prevent the development of more serious mental health problems [24].

As it is recommended for the prevention of depression during this stage [25], psychological interventions could be integrated into early childhood education classes, which would reduce the associated stigma and costs, and the benefits would extend to the baby before birth. During pregnancy, women frequently go to health services and are more willing to receive help because they believe it will have a positive impact on their baby [26]. However, there are barriers to accessing interventions during this period, such as lack of information about emotional problems, available and effective intervention options [27,28], as well as practical limitations of access to in-person treatment, such as costs, geographical distance, waiting lists or logistical problems such as attending appointments [26,27]. Furthermore, due to the stigmatization of mental health, especially during the perinatal period, women are reluctant to attend specialized mental health clinics in person [26,29].

The advances in information and communication technologies make it possible to have interventions via the internet, which can be carried out through computers, tablets or smartphones. These interventions may or may not be guided by a mental health professional, as well as being synchronous or asynchronous, that is, in real time or in deferred communication [30]. Furthermore, they have the advantage of helping to overcome the aforementioned barriers since they improve the acceptance of the intervention and are more flexible and accessible [30,31]. Systematic reviews of internet-based interventions during the perinatal period conclude that these interventions can reduce anxiety among mothers [32] and improve depressive and anxiety symptoms [31].

During the perinatal stage, interventions carried out through the internet represent a tool with great potential [33], as they tend to be more attractive since they reduce the need to travel—one of the barriers associated with low access to treatments for psychological problems during the perinatal period [30]. Peragallo-Urrutia et al. [34] found that 94.0% of pregnant and postpartum women use the internet, and 83% indicate their willingness to receive an online intervention in the perinatal period.

A form of therapy applied online is teletherapy, which has gained special importance since the COVID-19 pandemic. This form of treatment is carried out following a process similar to that of face-to-face therapy, although the interaction occurs electronically [35]. A systematic review of telepsychology [36] showed the effectiveness of different approaches, mostly based on the cognitive behavioral model, to reduce emotional distress. However, most of the research on the prevention of perinatal anxiety through the internet is unguided interventions, where participants access an application or web platform and view the material whenever they want and do not come in contact with an online healthcare professional at any moment, e.g., [37,38] or guided, where the participants, in addition to accessing the program material, have contact (via online and/or telephone) with a professional at some point during the intervention, e.g., [39,40]. To date, no protocol or study has been published on the effectiveness of cognitive behavioral therapy applied through video calls. Having an intervention developed through videoconferencing could help reduce the limitations of unguided therapies, since they do not offer direct interaction between the therapist and the patient, nor do they address the needs that may arise during said intervention [32].

On the other hand, it is worth remembering the high comorbidity of anxiety and depression. In a review and meta-analysis whose objective was to evaluate the effectiveness of psychological interventions to reduce perinatal anxiety, it was found that psychological interventions aimed at reducing anxiety during the perinatal stage were also effective in reducing symptoms of depression [7]. This supports research suggesting that transdiagnostic interventions targeting both anxiety and depressive symptoms tailored to the perinatal period may be more beneficial than disorder-specific interventions [37] and indicates the need to create transdiagnostic interventions to address symptoms of anxiety and depression in women during the perinatal stage since these comorbidities are generally not recognized or treated [41]. Therefore, considering the high frequency with which anxiety and depression occur together, treatments should treat them simultaneously [26].

To date, there is no protocol in Spain to prevent anxiety and comorbid emotional symptomatology during the perinatal stage by means of a videoconference psychological intervention. An intervention of this type could facilitate access and be helpful to many women during this period, reducing levels of anxiety and comorbid emotional symptoms.

The primary objective of the current study is to determine whether a preventive psychological intervention is superior to the usual care during pregnancy (attendance at pregnancy follow-up consultations and information and answers to frequently asked questions provided by the midwife) to prevent anxiety symptoms during pregnancy. The secondary objective is to examine whether this same intervention is more effective than usual care in preventing depressive symptoms during pregnancy, as well as anxiety and depressive symptoms postpartum.

